### Additional consent provisions for collection and use of participant data and biological specimens {26b}

On the actual day of blood specimen collection, the household heads/guardians will be presented with another consent form before a blood specimen is collected from the study children. If consent is obtained, then the field workers will collect the data. However, if consent is denied, blood specimens will not be collected from the child.

#### Interventions

##### Explanation for the choice of comparators {6b}

Long-lasting insecticidal nets (LLINs) will be the comparator in this study. This is because LLINs are the currently recommended intervention by the study countries’ NMCPs and by WHO. Universal coverage of LLINs for personal protection is also the gold standard malaria intervention and the only ethical comparator that can be used when testing new malaria control tools as has been demonstrated to be both effective and readily available. Therefore, we will ensure universal access to LLINs and then evaluate the additional benefits of house screening against malaria transmission.

#### Intervention description {11a}

##### House screening

In the target areas of all three countries, 400 houses will be screened with non-insecticide PVC-coated fiberglass netting by trained artisans recruited from each study village. The installations are expected to take about 2–3 months to complete. House residents will be trained on the care needed to keep the screens intact and avoid activities that could damage the screens. Screened houses will be examined by field assistants during entomological sampling of adult mosquitoes in sentinel households when conducting active case detection of malaria incidence every fortnight during the transmission season and during the cross-sectional parasite density surveys (parasite prevalence). The integrity of the screens will be recorded during these observations. Other routine procedures to reduce mosquito entry into houses, such as shutting the door whenever an occupant enters or leaves the house between 18.00h and 06.00h, will be emphasized and adherence to these practices monitored passively by the study field team during the above activities. These observations will be recorded in structured forms in order to quantify the frequency of their occurrence over time.

##### Criteria for discontinuing or modifying allocated interventions {11b}

Withdrawals may also occur if a study subject has any significant adverse events such increase in upper respiratory tract infections (URTis) in household members in screened households compared to non-screened households.

##### Strategies to improve adherence to interventions {11c}

Household heads and residents will be trained on the care needed to keep the screens effective, such as avoiding activities that may poke holes onto the nets or cause damages that will create spaces that would allow mosquito entry into the houses. Other routine procedures that reduce mosquito entry into houses such as closing windows and doors early will be emphasized and adherence to this practice monitored passively by the study team during entomological, clinical, and parasitological data collection as described above. The community members in the study areas will also be continually engaged on the benefits of participating in the study and the importance of following the recommended procedures above through community meetings to encourage adherence to malaria and parasitological surveys.

##### Relevant concomitant care permitted or prohibited during the trial {11d}

As this study aims to assess the additional impact of house screenings to LLINs in preventing malaria transmission, the use of IRS in the study target area will be prohibited.

##### Provisions for post-trial care {30}

At the end of the study, households in the control arm will be given the option of screening their households at project cost. Also, households in the intervention arm will be given the option of having the screens removed from their houses if they so wish.

#### Outcomes {12}

##### *Clinical endpoints*

The primary endpoint will be the incidence of clinical malaria in children between 6 months and 13 years. Clinical malaria will be assessed by active case detection over the main transmission season (January-April). The axillary temperature will be taken every fortnight by CHWs from all enrolled study children and if ≥ 37.5°C or history of fever in the past 48 h is reported, the child will be tested for malaria using a rapid diagnostic test kit (RDT). Blood specimens will also be collected using thick and thin blood slide smears for parasite identification and a dry blood spot (DBS) using a filter paper for later malaria analysis using PCR techniques.

The secondary endpoint will be the prevalence of malaria parasitemia in the study children, and the average parasite density in each study arm will be determined. Cross-sectional surveys will be done before (November) and after the main transmission season (May). A finger prick sample will be taken for an RDT and a thick and thin blood smear and DBS prepared for microscopy and molecular analysis in the laboratory.

RDT positive children will be provided with a full dose of *Artemether-lumefantrine* (AL) for treatment by a trained health worker following in-country national guidelines [47].

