As malaria risk may vary between villages, the number of intervention and control households per village will be balanced. A maximum of 10% of all households per village will be enrolled for house screening to avoid the potential diversion of mosquitoes from screened to non-screened households. A similar number of households will be assigned to the control arm in the same village so that the number of intervention and control households will be evenly distributed in each village across the study sites.

The main study outcome will be clinical malaria incidence monitored in the study children cohort by actively following each child enrolled in the study (active case detection-ACD), measuring their body temperature every fortnight for a period of 3–6 months during the high malaria transmission season (January to May) for 2 subsequent transmission seasons of the study. Children presenting with a fever above 37°C or reporting febrile illness in the past week will be tested for malaria using an RDT. The secondary outcome will be parasite prevalence assessed by screening study children at the beginning and end of each transmission season for the 2 consecutive transmission seasons of the study. Vector biting and resting densities indoors will be monitored throughout the study period using CDC light traps and PSC techniques in intervention and control sentinel houses. Acceptability of the proposed intervention, cost of house screening vis a vis LLINs, and the feasibility of scale-up to the community will be assessed using focus group discussions (FGDs) and key informant interviews (KII) with project stakeholders (Fig. 1).

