#### Participant timeline {13}

#### Sample size {14}

##### *Clinical*

The sample size used in this study is based on simulation models described in *Hayes and Bennet* et al. for incidence rates [50]. Routine data collected from all health facilities in Nyimba district in Zambia estimated an incidence rate of 0.312 cases per person from January to June 2019. Using these estimates in Eq. 1 [50], we estimated that in order to detect a reduction of 35% on malaria incidence, with 80% power at the 5% significance level, 338 houses were required per study arm when following one child per household per year [51]. A total of 400 households with one child each were recruited per treatment arm. The additional households were enrolled to account for households lost to follow-up.

Data collected from all health facilities in Chokwe district, Mozambique, estimated an incidence rate of 0.325 cases per person from January to June. Using the same formula, we estimated that 324 children were required per treatment arm to observe a 35% treatment effect with 80% power at the 5% significance level [50]. A total of 400 households were also recruited in Mozambique.
1$$ \mathrm{y}={\left({\mathrm{z}}_{\upalpha /2}+{\mathrm{z}}_{\upbeta}\right)}^2\left({\uplambda}_0+{\uplambda}_1\right)/{\left({\uplambda}_0\hbox{-} {\uplambda}_1\right)}^2 $$

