#### Adverse event reporting and harms {22}

Adverse events and serious adverse events will be recorded during both transmission seasons. Sick children will receive referral notes to the nearest health facility, and treatment will be documented.

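### Malaria treated and resolved between fortnightly visits is not counted in the primary endpoint, the sample size rests on facility cases, and the fever recall rule is stated in two conflicting ways

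*Protocol article*

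**What the plan says.** Outcomes, Clinical endpoints defines the endpoint: "The primary endpoint will be the incidence of clinical malaria in children between 6 months and 13 years". It names one detection method: "Clinical malaria will be assessed by active case detection over the main transmission season (January-April". The contact schedule follows: "The axillary temperature will be taken every fortnight by CHWs from all enrolled study children". The trigger for a test is an axillary temperature of at least 37.5°C, or the following: "history of fever in the past 48 h is reported, the child will be tested for malaria using a rapid diagnostic test kit (RDT".

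Trial design also describes fortnightly active follow-up, but with another trigger: "Children presenting with a fever above 37°C or reporting febrile illness in the past week will be tested for malaria using an RDT".

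Sample size, Clinical takes its control rate from a different source: "Routine data collected from all health facilities in Nyimba district in Zambia". That gives 0.312 cases per person for January to June 2019. Health facilities in Chokwe give 0.325 for the same months, with no year stated. Both rates enter Eq. 1 unadjusted.

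The article also foresees that ill children will be seen elsewhere. Adverse event reporting and harms says: "Sick children will receive referral notes to the nearest health facility, and treatment will be documented". That record is kept under harms. No section adds malaria diagnosed at a facility or by a community health worker between visits to the primary count.

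**The concern.** A visit every 14 days that looks back over a shorter period leaves part of each interval unobserved. An episode that begins, is diagnosed, treated and over before the recall window opens triggers no test and is not an event. Treated facility cases are the ones likely to be lost in this way, and they are also the kind of case behind 0.312 and 0.325. The trial plans on one kind of case and counts another.

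Three things are at stake.

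- **Precision.** Lost events reduce precision.
- **Absolute results.** Measured incidence and cases averted are understated. The cost-effectiveness endpoint derives DALYs from cases averted. If half of all episodes were captured in both arms, cases averted would halve and the cost per DALY averted would double, even with an unbiased rate ratio.
- **Consistency.** With two recall rules in one document, the share of episodes captured depends on which section field staff follow, and it could differ between countries.

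**Working it through.** **Inputs from the article.** Control rates 0.312 (Zambia) and 0.325 (Mozambique); 35% reduction; 80% power; 5% significance, two-sided as Eq. 1 is written; stated need of 338 and 324 per arm; 400 enrolled per arm; visits every 14 days; recall of 2 days (Outcomes) or 7 days (Trial design); two seasons.

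**Step 1: reproduce the plan's figures.** Eq. 1 is y = (z_α/2 + z_β)² (λ0 + λ1)/(λ0 − λ1)².

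- Zambia: λ1 = 0.65 × 0.312 = 0.2028, so y = 7.84 × 0.5148/0.1092² = 338.5 (stated: 338).
- Mozambique: λ1 = 0.65 × 0.325 = 0.21125, so y = 7.84 × 0.53625/0.11375² = 324.9 (stated: 324).

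The arithmetic is sound. Only the source of the rate is in question.

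**Step 2: share of episodes captured.** Assume an episode starts at a random point in the 14-day interval and is febrile for d days (the article gives no d). It is found if a visit falls during the fever or within w days after it ends. The share is c = (d + w)/14, capped at 1, with w = 2 or w = 7.

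**Step 3: power.** Multiply both arms' rates by c. Because (λ0 − λ1)²/(λ0 + λ1) = 0.35²λ0/1.65, power = Φ[√(N × 0.1225 × 0.312c/1.65) − 1.96]. N is 400 child-seasons per arm for one season and 800 for two, with no loss to follow-up and no correlation within a child.

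Worked case, d = 3, one season:

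- w = 2: c = 5/14 = 0.357; √3.309 − 1.96 = −0.14; power 44%.
- w = 7: c = 10/14 = 0.714; √6.618 − 1.96 = 0.61; power 73%.

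Zambia, 400 per arm:

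| Febrile days d | Captured, 48 h | Power, 1 / 2 seasons | Captured, 1 week | Power, 1 / 2 seasons |
|---|---|---|---|---|
| 2 | 29% | 37% / 63% | 64% | 69% / 93% |
| 3 | 36% | 44% / 73% | 71% | 73% / 95% |
| 5 | 50% | 58% / 86% | 86% | 80% / 98% |
| 7 | 64% | 69% / 93% | 100% | 86% / 99% |

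Full detection gives 86% for one season and 99% for two. Mozambique is close: at c = 0.5, one-season power is 59%.

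**Step 4: share needed for 80% power.** The required number scales as 1/c, so 400 per arm needs c ≥ 338.5/400 = 0.85 in one season, and two seasons need c ≥ 338.5/800 = 0.42. One-week recall gives at least 7/14 = 0.50, which is enough over two seasons for any d. With 48-hour recall, two seasons need d of about 0.42 × 14 − 2 = 3.9 days or more.

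**The case against.** The strongest reply is that active detection was chosen for good reason. House screening cannot be blinded, and visiting every child on the same schedule gives both arms equal ascertainment. Facility cases depend on care-seeking, which may differ by arm in an open trial. This stands as a caution: facility cases should be added only with test confirmation, attendance reported by arm and a visit-only sensitivity analysis. It does not justify leaving confirmed episodes out altogether.

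It can also be said that the full protocol may hold rules for linking facility records. Perhaps so, but the article itself names active detection as the method of assessment and uses facility rates unadjusted.

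A reader might infer more than the document supports:

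- **That only 2 of 14 days are covered, so a child ill from day 3 to day 8 is certainly lost.** This holds only under the Outcomes rule. Under the Trial design rule, a child seen on day 14 had fever within the past week and would be tested. The document does not settle whether that test would still be positive after treatment.
- **That the trial has 37% to 69% power.** Those are one-season figures under the narrower window. The trial follows two seasons. Active visits also find episodes that never reach a facility, and the facility rates are not stated to be for ages 6 months to 13 years. Nothing shows how far these offset the loss.
- **That the rate ratio is biased.** Under-capture that is equal in both arms need not bias it.
- **That the endpoint is really a point prevalence.** It is detection over repeated short windows, which is incomplete incidence.

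**Conclusion.** The concern holds in three limited parts. First, the primary endpoint as written omits test-confirmed episodes that are treated and resolve before the recall window. Second, the planning rates come from facility cases with no adjustment for the different detection method. Third, the recall window and fever threshold contradict each other between Outcomes (48 hours, at least 37.5°C) and Trial design (one week, above 37°C), and the two sections must be reconciled.

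The size is illustrative. It rests on an assumed fever duration, on true incidence equal to the facility rate, and on a follow-up season as long as the January to June period behind that rate. The choice of recall rule alone moves one-season power at three febrile days by 29 percentage points (73% − 44%), and two-season power by 22 (95% − 73%). The net effect on power cannot be determined from the document. The understatement of incidence and cases averted follows from the counting rule itself, although its size is also unknown.

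**What to change.** - State one fever threshold and one recall window, and use them in every section and on the visit form.
- At each fortnightly visit, ask whether malaria has been diagnosed since the last visit at a facility or by a community health worker. Copy the date and test result from the health card or register.
- Count each such test-confirmed case as a primary event, one per treated episode, with a post-treatment interval fixed in advance and removed from person-time.
- Keep the visit-only count as a sensitivity analysis, and report facility attendance by arm because the trial is open.
- In the sample size section, state that the rates come from facility data and for which ages, and show power over a range of capture rates.

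The cost is a few extra fields on an electronic form at visits already made, and some time checking records. Recruitment in Zimbabwe was still open, so the change can be made prospectively there. For any season already completed in Zambia or Mozambique, only a search of facility records could recover these cases, and the article does not say whether such records can be linked to cohort children.

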##### *Entomological endpoints*

The primary entomological endpoint will be the relative indoor mosquito density, expressed as the average number of mosquitoes caught per trap night in each study arm. The secondary endpoint will be the entomological inoculation rate (EIR) incorporating the blood meal source (human biting rate) and the mosquito sporozoite positivity per study arm.

A total of 30 sentinel houses per study arm (*N*=60) per country will be randomly selected for adult mosquito collections. The household selection will be stratified by village and geographical area so that an equal number of sentinel houses are selected in each village and equally spread over the study area. This stratified randomization by the village will reduce the likelihood of imbalances between study arms. Indoor host-seeking mosquitoes will be collected for 5 days each month using CDC UV light traps from 15 sentinel households. The CDC light trap will be placed next to the sleeping space of the study enrolled child and will be raised 1.5 m from the ground. The light trap will be set up at 7:00 p.m. and mosquitoes collected at 7:00 a.m. the next morning.

Indoor resting mosquitoes will be collected using pyrethrum spray catches (PSC) in the remaining 15 sentinel households in each arm of the study. The collections will be done inside the room where the child recruited into the study cohort sleeps. Mosquito sampling using PSC will be conducted early in the morning between 06:00 and 08:00 h. All the exit points to the sleeping area will be shut and a white sheet spread on the floor. An insecticide will then be sprayed in the room to knock down mosquitoes which will then be collected after 10 min. This sampling will be conducted 1 day for each month in the fixed sentinel households throughout the study period.

All the mosquito collections will be preserved in silica gel and transported to the respective national health laboratories where they will be stored in a freezer for identification using morphological and molecular methods. Morphological identification will use morphological keys for afro tropical vectors [48]. Molecular analysis of mosquito samples will be based on the polymerase chain reaction (PCR) to assess sporozoite infections in the mosquitoes and enzyme-linked immunosorbent assays (ELISA) for analysis of all blood-fed female *Anopheles* mosquitoes. A material transfer agreement (MTA) will be signed between the Ministries of Health of the project countries and *icipe* to allow for a sample of the collected mosquitoes to be transported to *icipe*, in Nairobi Kenya for quality assurance. In case there is no in-country capacity to process the collected samples, then all collected mosquitoes will be transported to *icipe* for morphological and molecular analysis.

##### *Cost-effectiveness endpoints*

To determine the cost-effectiveness of house screening, the costs associated with house screening will be collected from the implementing organizations (WHO and The NMCPs of the project countries). The per capita costs of house screening will be estimated by dividing the average cost of house screening per house by the household size, and this will be compared to the per capita costs of LLINs. Daily Adjusted Life Years (DALY) will be estimated for each household using standard methods on the basis of the number of malaria cases averted [49]. The cost-effectiveness ratio (CER) will be computed as the per capita costs of house screening per DALY averted.

The acceptability of house screening as a mosquito abatement tool will be evaluated using qualitative surveys that include key informant interviews and focus group discussions as the secondary endpoint.

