**Methods:**

A two-armed, household randomized clinical trial will be conducted in Mozambique, Zambia, and Zimbabwe to evaluate whether combined the use of house screens and LLINs affords better protection against clinical malaria in children between 6 months and 13 years compared to the sole use of LLINs. Eight hundred households will be enrolled in each study area, where 400 households will be randomly assigned the intervention, house screening, and LLINs while the control households will be provided with LLINs only. Clinical malaria incidence will be estimated by actively following up one child from each household for 6 months over the malaria transmission season. Cross-sectional parasite prevalence will be estimated by testing all participating children for malaria parasites at the beginning and end of each transmission season using rapid diagnostic tests.

CDC light traps and pyrethrum spray catches (PSC) will be used to sample adult mosquitoes and evaluate the impact of house screening on indoor mosquito density, species distribution, and sporozoite rates.

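### The cost-effectiveness ratio sets a per-person cost against DALYs defined per household, and does not say whose malaria cases enter the DALYs

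*Protocol article*

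**What the plan says.** The Cost-effectiveness endpoints paragraph of the Protocol article (Outcomes {12}) builds the ratio in three steps.

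1. Cost: "The per capita costs of house screening will be estimated by dividing the average cost of house screening per house by the household size". This figure is also to be compared with the per capita cost of nets.
2. Effect: "Daily Adjusted Life Years (DALY) will be estimated for each household using standard methods on the basis of the number of malaria cases averted".
3. Ratio: "The cost-effectiveness ratio (CER) will be computed as the per capita costs of house screening per DALY averted".

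On where the cases come from, the Abstract (Methods) says: "Clinical malaria incidence will be estimated by actively following up one child from each household for 6 months over the malaria transmission season". Trial design {8} and Sample size {14} likewise have one child per household. The primary clinical endpoint in Outcomes {12} is confined to children aged 6 months to 13 years.

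**The concern.** Step 1 divides by household size and step 2 does not. No later step does so either, and no other DALY quantity is defined. A ratio of the two therefore sets one person's share of the cost against the health gain of a whole house.

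A second question sits under the first: whose cases make up the household DALYs? The cost is spread over every resident, but clinical malaria is counted in one child of a limited age range. The text does not say whether the household figure is that child's DALYs, those of all eligible children, or those of all residents.

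The Discussion says the study will assess cost-effectiveness and is meant to support policy adoption of screening. A cost per DALY that is too low would mislead the readers for whom the ratio is intended.

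**Working it through.** The document gives no cost, household size, DALY weight or numerical ratio, so there is no figure to reproduce. The check is one of units, with an illustration.

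**Inputs**
- C, cost per house: not given; 100 currency units assumed.
- H, household size: not given; 3 to 8 assumed.
- n, residents aged 6 months to 13 years: not given; 2 or 3 assumed at H = 5.
- d, DALYs per case: not given; 0.02 assumed.
- a, cases averted per person: from Sample size {14}, Clinical, which "estimated an incidence rate of 0.312 cases per person from January to June 2019" and plans for a 35% reduction. So a = 0.312 × 0.35 = 0.1092 (illustration only).

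**Reading 1: DALYs are the household total**
- As written: CER = (C/H) / D_house.
- Matched units: CER = C / D_house, which equals (C/H) / (D_house/H).
- Matched divided by written = H. C and d cancel, so the factor does not depend on them.
- At H = 5, all members benefiting equally: D_house = 5 × 0.1092 × 0.02 = 0.01092. As written, 20 / 0.01092 = 1,831.5 per DALY. Matched, 100 / 0.01092 = 9,157.5 per DALY. The ratio is 5.0.
- Across assumed sizes the factor is 3, 4, 5, 6 and 8 at H = 3, 4, 5, 6 and 8.

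**Reading 2: household DALYs are the followed child's**
- D_child = 0.1092 × 0.02 = 0.002184.
- As written at H = 5: 20 / 0.002184 = 9,157.5 per DALY.
- If k members gain what the child gains, the house-level ratio is C / (k × D_child), and the understatement is H/k:

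| Members who benefit (k), H = 5 | House cost / household DALYs | Understatement of the ratio as written |
|---|---|---|
| 5 (everyone) | 100 / 0.01092 = 9,157.5 | 1.0 (none) |
| 3 (eligible children) | 100 / 0.006552 = 15,262.5 | 5/3 = 1.7 |
| 2 (eligible children) | 100 / 0.004368 = 22,893.8 | 5/2 = 2.5 |

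Under reading 2 the ratio is therefore correct only when the benefit to every resident equals that measured in the child.

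**The case against.** The best defence is that the ratio sentence says only per DALY averted, not per household. What the trial observes in each household is one person's malaria. Per capita cost over one person's DALYs is dimensionally sound, and on that reading the mismatch vanishes if the child represents the other residents. This stands as far as it goes: a reader might infer that the ratio is certain to be wrong by the full household size, and the document does not support that. But the defence needs equal benefit for unmeasured residents, adults included. The text states no such assumption, and its own words attach the DALYs to the household.

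Two further criticisms are tempting but fail.
- A reader might object that cases averted cannot exist for a single household, since each has only one allocation. The phrase "will be estimated for each household using standard methods on the basis of the number of malaria cases averted" can fairly be taken as an average per household from the between-arm difference. It needs clearer wording but is not an impossibility.
- A reader might infer that a one-off screening cost will be set unannualised against nets that are replaced periodically. The paragraph is silent on annualisation, and a condensed article may leave that to the full plan.

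It is also fair to say that the ratio has no bearing on the primary clinical comparison.

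**Conclusion.** The point holds as a flaw in a formula that the article itself prints, so it is not an omission excused by condensation. Taken literally, the ratio understates cost per DALY averted by a factor H, which is 4 to 6 at assumed household sizes of 4 to 6. If the household DALYs are the followed child's, the understatement is H/n when only eligible children benefit (1.7 to 2.5 at assumed H = 5, n = 3 or 2), and nil when all members benefit equally. Every size quoted rests on assumed H and n, because the document gives neither. The bias favours screening on the literal reading. On the other reading it does so whenever residents outside the measured age range gain less than the child. Which reading is intended cannot be settled from the text. The text should be corrected, but only the cost-effectiveness endpoint is affected; the clinical and entomological endpoints are not.

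**What to change.** Rewrite the paragraph so that both terms share one basis and the same follow-up period: either cost per house over DALYs averted per household, or per capita cost over DALYs averted per capita. In addition:

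- derive cases averted from the between-arm difference in incidence rates;
- state which household members' cases enter the DALYs;
- report any extension to ages in which malaria was not measured as a sensitivity analysis, with its assumption about benefit spelled out.

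The cost is a few lines of text. Household size is already needed for the planned per capita cost. Eligible children must already be listed in order to draw one at random, so their number should be available, although the questionnaire itself is in a supplement not seen here. The downside is that the ratio may come out less favourable to screening.

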## Introduction

### Background and rationale {6a}

Insecticide-based malaria control tools have led to significant reductions in malaria transmission, morbidity, and mortality in the past two decades [1]. However, recent reports indicate that progress in malaria control has stalled [2, 3] mainly due to the reallocation of funds previously available for malaria control, lack of political commitment to invest in malaria control programs and defined limits of current vector control strategies. That lack of adequate funding has resulted in the weakening of malaria control programs and the attendant coverage gaps of malaria interventions. One of the pillars of the Global Technical Strategy (GTS) [4] to reduce malaria morbidity and mortality by 90% globally is to ensure universal access to malaria prevention interventions [4] at an annually recurrent cost of between $6.4 and $8.7 billion from 2020 to 2030 [4]. In 2018, only $2.7 billion was invested in malaria control, about one third of the amount needed to attain the 2020 GTS targets [3]. Given the current COVID-19 pandemic [5] and its dire economic consequences worldwide, it is unlikely for this funding gap to be met any time soon. Consequently, the GTS goal of 90% coverage with currently supported malaria interventions will fall short, leaving a significant proportion of the at-risk population unprotected. This coverage gap may lead to a resurgence of malaria in regions where it had been previously been controlled and might jeopardize the elimination goal, especially in countries at the fringe of malaria transmission, like the Southern African Region [6]. Mathematical models estimate significant funding is needed to achieve the GTS strategy [4]. However, the return of investment of elimination (up to $300 billion) far outweighs the input costs, not to mention other costs saved from reduced malaria treatment and increase in the labor force from reduced illness [7]. Given the status of the world economy, it is unlikely that these funds will be available [8]. It is therefore prudent that financing mechanisms for malaria control are reviewed, adjusted, and diversified to fit the endemic countries that rely on international funding [9] and sustainable novel strategies for malaria control are developed for these settings [10].

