#### Socio-economic outcomes

##### Primary objective

To assess the incremental costs of house screening as a supplementary mosquito abatement tool.

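### The cost-effectiveness ratio is a gross programme-cost ratio: averted cases count as DALYs but earn no credit for the testing and treatment they would have used

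*Protocol article*

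**What the plan says.** The socio-economic primary objective is "To assess the incremental costs of house screening as a supplementary mosquito abatement tool". Under Cost-effectiveness endpoints, the article sets out each part of the ratio.

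- **Costs collected:** those of screening, obtained from WHO and the national malaria programmes.
- **Numerator:** "The per capita costs of house screening will be estimated by dividing the average cost of house screening per house by the household size".
- **Denominator:** DALYs, which "will be estimated for each household using standard methods on the basis of the number of malaria cases averted".
- **Ratio:** "The cost-effectiveness ratio (CER) will be computed as the per capita costs of house screening per DALY averted".
- **Nets:** of the screening cost per person the article says only that "this will be compared to the per capita costs of LLINs". Nets are compared with screens; no net cost is added or subtracted.

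No section collects the cost of malaria tests, drugs or facility care for this endpoint, or subtracts such costs. Under Clinical endpoints, each detected case involves a rapid test and a treatment course.

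**The concern.** A case that screening prevents has two economic consequences: health is gained, and a test and a treatment are not used. The stated formula counts the first and sets the second to zero. The result is a legitimate quantity, the programme outlay per DALY averted, but it is not the net cost per DALY averted. The article does not say which of the two is meant.

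The Discussion presents the cost-effectiveness work as support for policy adoption. A reader who compares this ratio with a net ratio for another malaria tool would see screening as dearer than it is. The direction of the error is known; its size depends on unit costs that the article does not give.

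**Working it through.** **Inputs from the Sample size section.** Facility incidence from January to June is 0.312 per person in Nyimba and 0.325 in Chokwe. The planned reduction is 35%, with 80% power and a 5% significance level.

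**Check that these inputs are coherent.** Equation 1 is n = (z_α/2 + z_β)² (λ0 + λ1) / (λ0 − λ1)², with λ1 = 0.65 λ0.

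- Zambia: λ0 + λ1 = 0.5148 and λ0 − λ1 = 0.1092, giving n = 338.8 (stated: 338).
- Mozambique: λ0 + λ1 = 0.53625 and λ0 − λ1 = 0.11375, giving n = 325.3 (stated: 324).

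With z rounded to 1.96 and 0.84, the results are 338.5 and 324.9, which round down to the stated figures. The inputs can be used.

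**Cases averted per child-season.** 0.312 × 0.35 = 0.109 in Zambia and 0.325 × 0.35 = 0.114 in Mozambique. Per 400 children that is about 44 and 46 cases a season.

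**Gross and net ratio.** Put cost and DALYs on the same per-person basis. Let C be the screening cost, A the cases averted over the horizon, c the test-and-treatment cost per case, and d the DALYs per case.

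- Gross ratio = C / (A·d)
- Net ratio = (C − A·c) / (A·d) = gross ratio − c/d
- Overstatement = c/d in dollars per DALY, or A·c/C as a share of the gross ratio

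**Size.** The article gives no value for c, C or household size, and none for d. The following are assumptions: c of $2 to $10, screening at $50 to $200 per house, and five people per house, so C is $10 to $40. Every household member is given the child rate, which makes the result an upper bound if older members have less malaria.

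Over two seasons:

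- Zambia: A = 0.2184, so the saving is $0.437 to $2.184 per person. The share runs from 0.437/40 = 1.1% to 2.184/10 = 21.8%.
- Mozambique: A = 0.2275, so the saving is $0.455 to $2.275 per person. The share runs from 0.455/40 = 1.1% to 2.275/10 = 22.8%.

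| Seasons of effect credited | Omitted saving as share of numerator, both sites |
|---|---|
| 1 | about 0.5% to 11% |
| 2 | about 1% to 23% |
| 5 | about 3% to 57% |

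The share scales with the number of seasons credited, so the time horizon matters as much as the unit costs.

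**The case against.** The strongest reply is that a gross ratio is a legitimate choice, openly defined, and that an article may leave the costing perspective and horizon to the full protocol. Much of this stands. Silence on perspective alone would be no finding. But the formula itself is written out, and as written it has no offset.

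A reader might infer several stronger claims, which the documents do not support.

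- **That the ratio fails the stated objective of incremental cost.** Nets are given in both arms: the abstract gives the intervention households screening and nets, "while the control households will be provided with LLINs only". Net cost therefore cancels, and the screening outlay already is the added cost of the tool. The objective mentions neither DALYs nor savings.
- **That the distortion is worst where malaria is most frequent.** In dollars per DALY the overstatement is c/d, which does not involve incidence. Only the percentage rises with incidence, because the gross ratio falls. With the same c and d, the ranking of settings is unchanged.
- **That the Background commits the plan to counting savings.** The phrase "not to mention other costs saved from reduced malaria treatment" belongs to a sentence on the overall return from elimination, not to this trial's costing.
- **That the programmes supplying the screening costs also pay for treatment.** The article says treatment follows national guidelines; it does not say who pays.
- **That counts of tests and referrals by arm would measure the saving.** Those counts reflect fortnightly active detection and surveys that test all study children, not routine use.

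**Conclusion.** The point holds in a limited form. The ratio is gross, and it overstates the net cost per DALY averted by c/d. The direction follows from the formula. The size does not follow from the documents: 1% to 23% of the numerator over two seasons rests on assumed costs of $2 to $10 per case and $10 to $40 of screening per person, on the planned 35% effect, and on the child rate applied to everyone in the household. At the low end it is negligible.

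The error makes screening look less favourable. The clinical endpoints are not affected, and the ratio can be supplemented at the analysis stage without changing trial conduct. This is a minor point and a cheap improvement.

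**What to change.** Under Cost-effectiveness endpoints:

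1. Keep the present ratio and label it as gross (programme cost only).
2. Add a net ratio whose numerator is screening cost minus the malaria test and treatment cost averted, on the same unit basis as the DALYs.
3. State the costing perspective, including whose treatment costs are counted, and the time horizon.
4. Compute averted cases by applying the trial's estimated effect to routine facility incidence of the kind used in the Sample size section, with programme unit costs. Do not use in-trial test or referral counts. The Sample size section gives no facility rate for the Zimbabwe site, so one would have to be obtained.
5. Vary the unit costs and the horizon in a sensitivity analysis.

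The cost is some extra wording, slightly more analysis work, and unit costs for testing and treatment. No additional participants, visits or samples are needed.
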